***End-point evaluation***

**Neurocognitive evaluation**

The neurocognitive evaluation will be done at baseline and after 2 months for all patients. In the cross group a 3^rd^ evaluation will be performed after 4 month- after crossing and completing 2 months of HBOT treatment. Cognitive function will be assessed using the one-hour Mindstreams Computerized Cognitive Test Battery (Mindstreams; NeuroTrax Corp., NY). Detailed description of the tests can be found on Neurotrax website ([www.neurotrax.com](http://www.neurotrax.com)).

To minimize differences in age and education, each outcome parameter will be normalized and fit to an IQ-like scale (mean=100, S.D=15) according to patient's age and education. Normalized subsets of outcome parameters will be aggregated to produce four index scores relevant to mild TBI: **Memory, Attention, Executive function,** and **Information Processing Speed**.

Three different test versions exist in the Mindstreams testing battery to allow repeated administrations, test-retest reliability for those versions were evaluated and found high, with no significant learning effect [[23](#_ENREF_23),[24](#_ENREF_24)].

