### Primary Efficacy Analysis Set

The primary endpoint parameter: *improvement in neurocognitive tests scores* will be measured following HBOT treatment for post TBI patients suffering from chronic neurocognitive deficiencies.

The primary efficacy analysis evaluation will include all subjects who completed the HBOT treatment or the control period, had no major protocol violations, and for whom there is a valid *mindstreams score* at baseline and following 2 months of HBOT treatment.

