**Sample Size Considerations**

Presentation of sample size is based on achieving 80% power overall to demonstrate that improvement rate in *mindstreams score* is at least 12%. An improvement rate of at least 10% in the neurocognitive score in treatment group (compared to baseline, prior to HBOT treatment) would be an appropriate clinical target for HBOT treatment success and of sufficient interest to encourage further investigation of HBOT treatment for post TBI patients suffering chronic neurocognitive deficiencies.

Sample size is based on the assumption that exposure to the *mindstreams* tests at baseline without any additional training might induce 2% score improvement in the second test, following treatment, (test-retest effect). Assuming a true success rate of 12% a sample of N = 31 will provide 80% power to show that HBOT treatment induces at least 10% improvement on *neurocognitive test score*. This is based on a power analysis using the normal approximation for the binomial, with one-sided Alpha=0.05.

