### Primary Efficacy Analysis

For the primary end point, Neurocognitive function (using Mindstreams neurocognitive battery test score), we will compute Overall Proportion of Success:

The following hypotheses are specified and will be tested separately:

For Neurocognitive *tests score* proportion of improvement:

H_0_: p_1=_ p _2_

H_1_: p_1>_ p_2_

While p1= Neurocognitive function (using Mindstreams neurocognitive battery *tests score*) improvement as a result of the HBOT training (assumed to be 0.12); and

p2= Neurocognitive function (using Mindstreams neurocognitive battery *tests score*) improvement as a result of test-retest effect (assumed to be 0.02)

This hypothesis will be tested by:

1. Constructing a one-sided, lower 95% confidence interval about the observed Overall Proportion of Success in the relevant cohort.
2. Examining whether the lower limit of the confidence interval is at or above the success criterion

Study success will be declared if the following is met:

1. Lower confidence limit of HBOT treatment success is at 0.12 or above

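### The primary success rule tests a share of patients without saying what makes a patient a success, and uses percent score gains as that share, so its stated 5% error is not delivered

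*Protocol*

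**What the plan says.** The Protocol's Primary Efficacy Analysis Set section gives the endpoint in general terms: "The primary endpoint parameter: *improvement in neurocognitive tests scores* will be measured following HBOT treatment". No size of gain is attached to it.

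The Primary Efficacy Analysis section tests H0: p1 = p2 against p1 > p2. It takes p1 as "improvement as a result of the HBOT training (assumed to be 0.12" and p2, the retest value, as 0.02. The test is carried out by "Constructing a one-sided, lower 95% confidence interval about the observed Overall Proportion of Success in the relevant cohort", and the trial succeeds if "Lower confidence limit of HBOT treatment success is at 0.12 or above".

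The Sample Size Considerations section shows where these values come from. The 2% is introduced as a rise in score on second exposure to the test. A 10% improvement in the treatment group's score against baseline is the clinical target. The same section then treats 12% as a rate of success: "Assuming a true success rate of 12% a sample of N = 31 will provide 80% power", using the "normal approximation for the binomial, with one-sided Alpha=0.05".

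The Neurocognitive evaluation section describes a continuous score: "each outcome parameter will be normalized and fit to an IQ-like scale (mean=100, S.D=15) according to patient's age and education". The parameters are combined into four index scores. It calls retest reliability high but gives no figure.

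**The concern.** A binomial rule needs a yes/no definition for each patient, and the Protocol gives none. Its two proportions are percent changes in a score, moved onto a scale where they mean something else. A mean gain of 2% in a continuous score with retest error says nothing direct about how many patients gain. That share depends on the cut-off and on the spread of the retest change, and the Protocol fixes neither.

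This rule alone declares study success. If its untreated value and its bar do not correspond to any stated definition of success, its false-positive rate is unknown. The definition could also be settled after results from an open-label comparison have been seen. The rule makes no use of the randomised control period either, although the hypothesis it claims to test compares two groups.

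**Working it through.** **Inputs from the Protocol.** One-sided alpha 0.05, 80% power, N = 31 (not stated whether total, per arm or HBOT-treated), p1 = 0.12, p2 = 0.02, bar 0.12, score SD 15, mean retest gain 2%, 10% target.

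**Assumed.** Retest correlation r from 0.6 to 0.9; baseline score B from 85 to 100; normally distributed change; SD 15 applies to the analysed score.

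**1. The plan's own N.** One-sample normal approximation: n = [z(1-α)·√(p0(1-p0)) + z(0.80)·√(p1(1-p1))]² / (p1-p0)², with p0 = 0.02 and p1 = 0.12. The square roots are 0.140 and 0.325.
- α = 0.05 one-sided: (1.645×0.140 + 0.842×0.325)² / 0.01 = 25.4, so 26.
- α = 0.025 one-sided: (1.960×0.140 + 0.842×0.325)² / 0.01 = 30.02, so 31.

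The stated 31 is reproduced only at the stricter alpha, which is a separate matter. What counts here is that the figure comes from treating 0.02 and 0.12 as binomial shares of patients.

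**2. Successes needed at n = 31.** The interval method is not named.
- 8/31 = 0.258: Wald limit 0.258 - 1.645·√(0.258×0.742/31) = 0.129; exact limit 0.135. Both pass.
- 7/31 = 0.226: Wald 0.102, exact 0.111. Both fail.

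So 8 are needed (7 with the Wilson score limit).

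**3. Untreated share of successes.** Let the change be normal with mean 0.02B and SD s = 15·√(2(1-r)).
- Any rise: share = Φ(0.02B/s).
- Gain of at least 10%: share = 1 - Φ((0.10B - 0.02B)/s).

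Example, B = 90 and r = 0.8: s = 9.49. Any rise: Φ(1.8/9.49) = 0.575. At least 10%: 1 - Φ(7.2/9.49) = 0.224, and P(X ≥ 8 | 31, 0.224) = 0.39.

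Ranges over B = 85 to 100, n = 31, 8 needed:

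| r | s | Share, any rise | Rule met | Share, ≥10% | Rule met |
|---|---|---|---|---|---|
| 0.6 | 13.4 | 0.55-0.56 | >0.999 | 0.275-0.306 | 0.65-0.78 |
| 0.7 | 11.6 | 0.56-0.57 | >0.999 | 0.246-0.279 | 0.50-0.67 |
| 0.8 | 9.5 | 0.57-0.58 | >0.999 | 0.200-0.237 | 0.27-0.46 |
| 0.9 | 6.7 | 0.60-0.62 | >0.999 | 0.117-0.155 | 0.02-0.10 |

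With no retest gain at all, the any-rise share is 0.50 and the rule is met with probability 0.998. If only 15 patients are treated, 5 are needed and the probability is 0.94.

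**4. Smaller SD, 10% cut-off.** An average of imperfectly correlated parameters has a smaller SD unless it is re-normalised.
- SD 12: rule met 0.07-0.20 at r = 0.8, and 0.001-0.011 at r = 0.9.
- SD 10: rule met 0.01-0.06 at r = 0.8, and below 0.001 at r = 0.9.

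**5. What 0.02 would require.** At B = 100 and SD 15, only 2% of untreated patients exceed a cut-off of 2 + 2.054·s. That is 15.8 points at r = 0.9 and 29.6 points at r = 0.6. The Protocol states no such cut-off. If the untreated share really were 0.02, the rule would be met with probability below 0.0001.

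**The case against.** A reader might infer that any rise counts as success, so that about half of untreated patients succeed by chance and the trial is almost certain to declare success whatever HBOT does. The Protocol does not support that. No section says any rise counts, its own retest value of 0.02 could not hold under that reading, and the Sample Size Considerations section names a 10% target that can be read as a cut-off. The near-certain false positive belongs to one reading only.

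Under the 10% reading, the large figures need a retest correlation of 0.6-0.7, which fits poorly with reliability described as high. SD 15 is stated for each outcome parameter, not for the aggregated index. With high reliability or a smaller index SD, the false-positive rate can be near or below 5%. These points stand, and they rule out saying that the rule cannot tell an effective treatment from an ineffective one.

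It may also be said that a definition of success belongs in a statistical analysis plan. That does not answer the point. The Protocol itself fixes the statistic, the untreated value, the bar and the sample size, and the numbers are of the wrong kind. Moreover, the 10% wording refers to the score in the treatment group, and the analysis section never mentions it.

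**Conclusion.** The concern holds as a defect in how the rule is specified. Success is undefined for the individual patient, and percent score gains are used as shares of patients. The chance of declaring success with no HBOT effect then depends on the missing definition: over 99% if any rise counts; 2-78% with a 10% cut-off per patient at SD 15, retest correlation 0.6-0.9 and baseline 85-100; and close to 0 if the index SD is smaller and reliability high. The one-sided 5% error is not a property of the rule as written. Correlation, baseline score and the SD of the index are assumptions. The mismatch between score gains and patient shares rests on the text alone. Because this rule decides the trial, it must be corrected before the analysis.

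**What to change.** In Sample Size Considerations and Primary Efficacy Analysis:

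- Stop using 0.02 and 0.12 as shares of patients.
- Name the Mindstreams index score that decides the primary analysis, and a minimum gain per patient fixed in advance, for example the 10% target the Protocol already gives.
- Replace the one-sample rule by a direct one-sided 5% test of H0: p1 = p2. Compare the treated group's month 0-2 success share with the cross group's share over its untreated months 0-2.
- If 2% and 12% were meant as mean score gains, compare mean change between the randomised groups, adjusted for baseline, instead.
- Restate the power for the test chosen.

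Do not set the cut-off as mean plus 1.645 SD of the change in about 15 control patients and then assume a 5% untreated share. In simulation with normal changes and no effect, the average untreated share was 6.7%. An exact one-sided lower-limit rule against 5% was met 11% of the time with 15 treated patients and 12% with 31.

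The cost is rewording and a new power calculation. The control-period data are already collected, so the change calls for no extra patients or visits. The downside is that the stated 80% power at N = 31 may not hold. As an indication only, detecting shares of 0.12 against 0.02 in a two-group one-sided test would take about 80 per arm, so the power must be restated openly.

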**Randomization**

Since the diversity of the patients included in the study, after signing the informed consent is expected to be high, no stratifies criteria will be used. Patients will be randomized in 1:1 fashion to either treatment or controlled-cross group.

There will be no placebo in the cross group during the control period. The only way to give “placebo” of HBOT, is to bring the patients to the hyperbaric chamber and to increase the environmental pressure in a way the patients will “feel the hyperbaric pressure” in their ears. However, Henry’s law states: “the amount of a given gas dissolved in a given type and volume of liquid is directly proportional to the pressure of that gas in equilibrium with that liquid”. Thus, hyperbaric environment significantly increases the dissolved oxygen pressure even if a person holding his breath [[29](#_ENREF_29)]. Moreover, the alternative of hosting the patients in the hyperbaric chamber without any pressure increase cannot serve as a real placebo since the patients will not feel the pressure. Accordingly, the only real “placebo” could be achieved by increasing the pressure and reducing the percentages of the oxygen but that holds significant safety consideration.

From the ethical point of view, it is deemed unethical to “treat” the patients (40 sessions in the hyperbaric chamber) while they actually know that it is a placebo. In order to somewhat compensate for this limitation, the control will be a cross group and after the 2^nd^ evaluation at the end of a control period they will be crossed to HBOT. The cross for treatment enables intra-group efficacy evaluation in both treatment and control group.

Since the patients will know they are not receiving HBOT during the control period they will not be blinded with regard to the treatment arm. Accordingly, the quality of life evaluations will not be blinded. However, the complete blindness evaluation can be assured in both of the primary end points of this study, The Mindstreams computerized evaluation and the brain SPECT evaluation done by the radiologist.

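### The primary success rule judges HBOT against a fixed 0.12 in one group; the randomised control group's measured month-2 change enters neither the test nor the sample size

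*Protocol*

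**What the plan says.** All citations are to the Protocol.

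- **Design.** Study protocol and Randomization describe 1:1 allocation to HBOT or a control-cross group. Both groups are tested at baseline and month 2. The cross group is untreated in that interval, then receives HBOT and is tested a third time at month 4.
- **Hypothesis.** Primary Efficacy Analysis sets p1 equal to p2 under the null. p1 is "improvement as a result of the HBOT training (assumed to be 0.12"); p2 is "improvement as a result of test-retest effect (assumed to be 0.02").
- **Test.** The procedure is "Constructing a one-sided, lower 95% confidence interval about the observed Overall Proportion of Success in the relevant cohort". The success criterion is "Lower confidence limit of HBOT treatment success is at 0.12 or above".
- **Sample size.** Sample Size Considerations says that exposure to the tests at baseline "might induce 2% score improvement in the second test", sets the clinical target against the treated group's own baseline, and gives N = 31 for 80% power. It adds: "This is based on a power analysis using the normal approximation for the binomial, with one-sided Alpha=0.05".
- **Stated purpose of the crossing.** Randomization says: "The cross for treatment enables intra-group efficacy evaluation in both treatment and control group".

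The protocol states no primary comparison of the HBOT group with the control period.

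**The concern.** A before-after result in one group cannot separate the treatment from whatever else changes over two months: familiarity with the tests, natural change, and regression to the mean in patients enrolled because they complain of deficits. The control period measures the sum of these in randomised patients. The written rule replaces that measurement with constants, so the verdict is the same whether the control group improves as much as the HBOT group or not at all.

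The constants also disagree. The hypothesis and the sizing work from 0.02, whereas the success criterion works from 0.12, which is also the assumed true HBOT rate.

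A claim of efficacy from a randomised trial would therefore rest on an uncontrolled comparison.

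**Working it through.** **Inputs from the protocol:** p1 = 0.12, p2 = 0.02, success limit 0.12, one-sided 95% limit, N = 31, 80% power. The protocol does not say whether 31 is the total or per group, and does not define success for a single patient. The binomial figures below treat 0.12 and 0.02 as proportions of patients, as the protocol's own power method does.

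**1. The protocol's N.** One-sample normal approximation:

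n = [(z_α√(p0(1−p0)) + z_β√(p1(1−p1))) / (p1−p0)]², with p0 = 0.02, p1 = 0.12

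- One-sided 0.05, as stated: [(1.645×0.140 + 0.842×0.325)/0.10]² = (0.5038/0.10)² = 25.4, so 26.
- One-sided 0.025: [(1.960×0.140 + 0.842×0.325)/0.10]² = (0.5479/0.10)² = 30.02, so 31.

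N = 31 is thus a one-sample figure, matched at one-sided 0.025 rather than the stated 0.05.

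For two arms, with mean proportion 0.07, at one-sided 0.05: n per arm = [(1.645√(2×0.07×0.93) + 0.842√(0.12×0.88 + 0.02×0.98))/0.10]² = (0.8913/0.10)² = 79.4, so 80. No control arm entered the sizing.

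**2. What the 0.12 rule requires.**
- 7/31 = 0.226: lower limit 0.102 (Wald) or 0.111 (exact). Fails.
- 8/31 = 0.258: 0.258 − 1.645×0.0786 = 0.129 (Wald) or 0.135 (exact). Passes.

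At least 8 successes are needed. (A Wilson limit would pass at 7.) If the true HBOT rate is the assumed 0.12, P(X ≥ 8) = 2.7%, which shows how far the criterion lies from the 80% power calculated against 0.02.

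**3. False success with no HBOT effect.** P(X ≥ 8 | n = 31, q), where q is the success rate without treatment. Each q is an assumption.

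| q | P(declare success) |
|---|---|
| 10% | 1.0% |
| 15% | 8.2% |
| 20% | 27% |
| 25% | 53% |
| 30% | 76% |

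**4. What q might be.** Suppose success means a gain of at least 10% on the patient's own baseline. Assume bivariate normal scores with mean 90, SD 15 and a retest gain of 0 to 2 points; none of these is in the protocol. The retest correlation r is varied. Simulated results:

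| r | untreated success rate, gain 0 to 2 | P(at least 8 of 31) |
|---|---|---|
| 0.95 | 4% to 9% | 0% to 0.5% |
| 0.90 | 11% to 17% | 1% to 13% |
| 0.80 | 19% to 24% | 20% to 49% |
| 0.70 | 23% to 28% | 43% to 69% |

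**5. Power of the comparison that is missing.** For 0.12 against 0.02 with 31 per arm, one-sided 0.05: Φ[(0.10 − 1.645×0.0648)/0.0636] = Φ(−0.10) = 46%. If 31 is the total (15 to 16 per arm), the power is 28% to 29%.

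**The case against.** The best defence is that the null hypothesis names two proportions, that the Primary Efficacy Analysis Set admits patients who completed either HBOT or the control period, and that an analysis plan may add the comparison. But p2 is defined as an assumed retest effect, not as the control group's result, and the procedure is one interval on one proportion. The protocol fixes this rule itself, so the point is not one left for the analysis plan.

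Other objections do stand, and they limit what may be inferred.

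- **That HBOT is tested against 2%.** A reader might take 0.02 as the decision limit. On that reading at least 3 of 31 successes suffice, and false success is 20% and 61% at untreated rates of 5% and 10%. The written limit is 0.12, so these figures do not describe the rule.
- **That a false positive is likely.** The documents do not support this. If 10% of untreated patients succeed, the rule errs about 1% of the time. Neurocognitive evaluation reports high test-retest reliability, and at a correlation of 0.95 the error is at most about 0.5%.
- **That the protocol contradicts itself on learning.** It says the three test versions were found reliable "with no significant learning effect", yet allows 2%. A non-significant effect and a small cautious allowance are compatible. The 2% is framed for the second test, whereas the cross group's post-HBOT test is its third, but a version exists for each of the three.
- **That the randomisation is worthless, or that using it would remove expectation effects.** The control data are collected; the rule does not use them. Because the control is open-label with no sham, a between-arm difference would still contain expectation.

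**Conclusion.** The point holds. The primary decision is a one-group confidence limit against a fixed 0.12, in conflict with a hypothesis and sample size built on an assumed 0.02, and the randomised control cannot affect it. This follows from the text alone and needs no assumption.

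The size of the harm does need assumptions: a per-patient meaning of success, n = 31, and an untreated success rate or a retest correlation. Across the values examined, false success runs from near 0 to about 76%. The protocol gives no basis for choosing a value in that range, whereas the control group would measure it. A retest effect up to the assumed 2% is nominally allowed for in the hypothesis; anything beyond it, together with natural change and regression to the mean, is credited to HBOT. This should be corrected before the primary analysis.

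**What to change.** - Make the primary analysis the randomised comparison of HBOT with control at month 2: ANCOVA of the Mindstreams score on arm, adjusted for the baseline score. Judge success on the confidence limit of the between-arm difference. Neurocognitive evaluation produces four index scores, so say which score or scores are primary.
- Remove 0.02 and 0.12 as test constants; keep them as planning figures only.
- Report within-group changes, including the cross group's month 2 to month 4 change, as supportive.
- Reword the Primary Efficacy Analysis Set. It requires a score after two months of HBOT, which for the cross group is the month-4 test, not the month-2 test that the comparison needs.

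**Cost.** No new visits or measurements are needed, but this is more than a change of wording. The standard error of a between-arm difference is larger than that of one group's change, partly recovered by the baseline adjustment. The statement of 80% power with N = 31 must be replaced. As proportions, 0.12 against 0.02 needs about 80 per arm at one-sided 0.05. For a continuous outcome with a difference of 10 points, the need is 13 to 78 per arm at one-sided 0.05 if the SD is 10 to 25 points, without baseline adjustment; the protocol gives no SD, so that range is an assumption. Expectation effects remain and should be stated as a limitation.

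### The success rule sets the lower confidence limit against 0.12, the assumed true value itself, so under the protocol's own assumption the trial succeeds about 5% of the time, not 80%

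*Protocol*

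**What the plan says.** In the Protocol, Primary Efficacy Analysis, the null hypothesis is p1 = p2 and the alternative is p1 > p2. The two quantities are defined as "improvement as a result of the HBOT training (assumed to be 0.12") and "improvement as a result of test-retest effect (assumed to be 0.02"). The test is made by "Constructing a one-sided, lower 95% confidence interval about the observed Overall Proportion of Success in the relevant cohort", and the only success criterion is: "Lower confidence limit of HBOT treatment success is at 0.12 or above".

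Sample Size Considerations uses the same 12% as the assumed truth: "Assuming a true success rate of 12% a sample of N = 31 will provide 80% power". The calculation is described as a "power analysis using the normal approximation for the binomial, with one-sided Alpha=0.05". That section opens by giving 12% as the rate to be demonstrated. It then names a clinical target, "An improvement rate of at least 10% in the neurocognitive score in treatment group", and ends by saying that the 80% power is for showing at least 10%. It also allows 2% for the test-retest effect.

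**The concern.** A lower confidence limit tests a null hypothesis when it is compared with the null value. Here it is compared with the value assumed under the alternative. A rule cannot have 80% power at a true rate of 0.12 and also require the lower limit to reach 0.12, so the two sections cannot both hold.

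This is the only success criterion given for the neurocognitive primary endpoint. If it is followed literally, a treatment that performs exactly as assumed will almost certainly be declared a failure. If it is set aside at analysis, the threshold will be chosen with the data in hand, and the text offers more than one candidate figure.

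**Working it through.** **Inputs.** From Primary Efficacy Analysis: p1 = 0.12, p2 = 0.02, one-sided 95% lower limit, success threshold 0.12. From Sample Size Considerations: N = 31, 80% power, one-sided alpha 0.05, normal approximation to the binomial, clinical target 10%.

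**1. Which null value lies behind N = 31?** For one sample,

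n = [(z_alpha·√(p0(1−p0)) + z_power·√(p1(1−p1))) / (p1−p0)]²

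with p1 = 0.12, √(0.12·0.88) = 0.325 and z_power = 0.842.

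- p0 = 0.02, one-sided 0.05: [(1.645·0.140 + 0.842·0.325)/0.10]² = 25.4, so 26. Power at N = 31 is 84.2%.
- p0 = 0.02, one-sided 0.025: [(1.960·0.140 + 0.842·0.325)/0.10]² = 30.02, so 31. Power at N = 31 is 80.8%.
- p0 = 0.10, one-sided 0.05: [(1.645·0.300 + 0.842·0.325)/0.02]² = 1,470.5, so 1,471.
- p0 = 0.12: the denominator is zero, so no N exists.

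The stated N is reproduced with 0.02 as the null value, though at one-sided 0.025 rather than the stated 0.05. That difference makes N conservative and does not affect this point.

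**2. The rule as written, true rate 0.12.** By normal approximation, the probability that the lower limit is at or above the true value is 5.0% at any N. For a binomial count, find the smallest r whose lower limit is at least 0.12, then compute P(X ≥ r | N, 0.12).

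| N | Interval | Smallest r | P(success) |
|---|---|---|---|
| 31 | Clopper-Pearson or Wald | 8 (25.8%) | 2.7% |
| 31 | Wilson | 7 (22.6%) | 7.1% |
| 100 | Clopper-Pearson or Wald | 19 | 2.8% |
| 100 | Wilson | 18 | 5.1% |
| 500 | Clopper-Pearson or Wald | 73 | 4.6% |
| 500 | Wilson | 72 | about 6% |

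Enlarging the trial does not help. At N = 31 this rule has 80% power only if the true rate is about 0.31 (r = 8) or 0.28 (r = 7).

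**3. Threshold at p2: lower limit above 0.02, N = 31, true rate 0.12.**

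| Interval | Smallest r | Power at 0.12 | P(success) at 0.02 |
|---|---|---|---|
| Clopper-Pearson | 3 | 73.6% | 2.4% |
| Wald | 4 | 52.0% | 0.3% |
| Wilson | 2 | 90.1% | 12.7% |

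The Wilson figure is bought with an error rate well above 5%. The choice of interval therefore matters at this sample size.

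**4. Threshold at 0.10, N = 31, true rate 0.12.** The probability of success is about 12% by normal approximation, and 7.1% to 16.1% exactly, depending on the interval.

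**5. Randomised comparison, 0.12 against 0.02, one-sided 0.05.** With 31 per arm the pooled rate is 0.07. The standard error is √(0.07·0.93·2/31) = 0.0648 under the null and √((0.1056 + 0.0196)/31) = 0.0636 under the alternative. Power = Φ[(0.10 − 1.645·0.0648)/0.0636] = Φ(−0.10), about 46%. With 31 in total (15.5 per arm) the same formula gives about 29%. An 80% power target needs about 80 per arm.

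**The case against.** The best defence is that 0.12 is deliberate. The clinical target is 10%, the retest allowance is 2%, and 10% + 2% = 12%. The first sentence of Sample Size Considerations also gives 12% as the rate to be shown. On that reading the threshold is right, and the assumed true rate and N are what is wrong. This stands as far as it goes: the protocol does not settle which element is in error. It does not remove the contradiction, because the same section assumes a true rate of exactly 12% and claims 80% power.

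A reader might also infer that three rival success thresholds are in force. That goes too far. The 10% can be read as the net effect, 12% less 2%, and Primary Efficacy Analysis states only one success threshold.

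A reader might infer that success can never exceed 5% under the assumption. That is guaranteed only for an interval with assured coverage, such as Clopper-Pearson. The protocol names no interval method, and the Wilson limit gives 7.1% at N = 31. About 5%, or 3% to 7% at N = 31, is the supportable statement.

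Finally, the counts out of 31 treat the endpoint as a responder proportion, while the protocol also speaks of a 2% improvement in score. If 0.12 is a mean percent change, the counts and the required true rates in step 2 fall away. The level of roughly 5% does not.

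**Conclusion.** The concern holds. With the threshold equal to the assumed true value, the probability of success at N = 31 is 2.7% to 7.1% against a stated 80%, and no sample size repairs this. The result rests only on the protocol's assumed 0.12 and its one-sided 95% limit. The exact percentages also assume a responder proportion and depend on the interval method.

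The value 0.02 is the best-supported benchmark, because it is the p2 of the stated hypothesis and the only stated value that reproduces N = 31. It is tempting to go further and say that 0.02 is proven to be what the sponsor intended, or that moving to it restores 80% power. The documents support neither. The text also speaks of showing 12% and 10%, and exact power at 0.02 ranges from 52% to 90%. Nor can a switch to an HBOT-minus-control rule be presented as free, since N = 31 matches a one-sample calculation.

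**What to change.** Make the success threshold match the null value used for the power calculation. On the figures given, the rule becomes: *success is declared if the one-sided 95% lower confidence limit is above 0.02*. Name the interval method and restate the power at N = 31 for that method (step 3). Align the 10% and 12% wording in Sample Size Considerations with the rule.

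If the sponsor does mean to show at least 12%, the assumed true rate and the 80% claim must be restated. If the aim is at least 10% with a true rate of 12%, about 1,471 patients are needed.

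A randomised HBOT-minus-control comparison at 2 months, with the lower limit of the difference above 0, would test p1 = p2 more directly and use the existing control group. Its power must then be stated as it is: for proportions of 0.12 and 0.02, about 46% with 31 per arm and about 29% with 31 in total. The protocol does not say which of these N = 31 means.

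The cost of the first option is a short amendment with a named interval and a restated power. It needs no new procedures, but it may need more patients if 80% exact power is to be kept. The other options change the sample size or the power claim.
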